**Table 1 T1:**
[figure not shown]
Data collection schedule.

The VAS has been used extensively for rating pain intensity in previous studies.^[15–17]^ Postoperative pain at 6, 12, 24, 36, 48, and 72 hours after surgery will be recorded using the VAS pain scores. The VAS consists of a 10-cm horizontal line with 1-cm vertical lines at each end on which a score of 0 indicates no pain and a score of 10 indicates the worst conceivable pain. All data are verified against original documents by individuals who are independent of the trial.

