### Sample size

2.17

The sample size calculation was based on the following parameters:

(1)alpha value = 0.05, 2-sided;(2)power = 80%.

The minimal clinical significance in VAS pain score was defined as the mean difference between current and preceding scores when the subject reported “a little worse” or “a little better” pain. Our pilot study shows that VAS pain scores 72 hours after lumbar spinal fusion surgery were reported to be 2.1 ± 1.6 in patients receiving cocktail analgesic injection and 5.6 ± 1.7 in patients without. Based on these findings, we hypothesized that VAS pain score 72 hours after surgery will be 2.5 for the cocktail group and 5.0 for the control group, with a standard deviation set at 2.5 and a ratio of patients in the cocktail to the control group of 1:1. Calculations showed that a sample size of 14 patients per group to detect a difference in VAS pain score between the 2 groups after treatment. Assuming a 20% dropout rate, 18 patients per group, or a total of 36 patients, are required.

It is anticipated that recruitment for this study will take 6 months to complete, using 1 surgeon to reduce surgical variability. Data collection for each patient will occur during the first 72 hours postoperatively and at a routine 4-week follow-up appointment. No further follow up will be routinely arranged. Any patients requiring specific follow up will have this arranged on an individual basis.

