To determine changes of analgesic consumption and pain score over time between groups, a generalized estimating equation population average regression will be used. To correct for ceiling effect of analgesic consumption on pain score reporting, an empirical logit transformation will be applied in before comparison between groups. For missing data less than 10%, imputation will be performed using median for continuous and ordinal variables. For nominal variables, the most common category will be imputed. If there are more than 10% missing data, multiple imputation will be used. Intention-to-treat and per-protocol analyses will be performed to account for possible missing data. *P*-value less than .05 will be considered as statistical significance. All statistical analyses will be 2-tailed and performed using Statistical Package for Social Sciences (SPSS version 24.0, Chicago, IL).

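### GEE for pain over time in 28 to 36 patients: with the usual uncorrected robust Wald chi-square test, the joint group-by-time test would have a false-positive rate of about 13–17%, not 5%

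*Protocol article*

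**What the plan says.** In the Protocol article, Data analysis (2.21), the comparison between groups of pain score and analgesic consumption over time is assigned to one method: "a generalized estimating equation population average regression will be used". The threshold is a P "value less than .05 will be considered as statistical significance", two-tailed, in SPSS 24. An empirical logit transformation is to be applied first.

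The data for that model are described elsewhere. Data capture (2.14.1) states: "Postoperative pain at 6, 12, 24, 36, 48, and 72 hours after surgery will be recorded using the VAS pain scores". Sample size (2.17) gives "a sample size of 14 patients per group", raised to 18 per group and 36 in total for 20% dropout.

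The article does not state the working correlation, robust or model-based standard errors, whether time is linear or categorical, or the reference distribution. The primary outcome (2.15) is one average score per patient up to day 3. Data analysis gives Student t or Mann–Whitney for group comparisons. GEE is not named as the primary analysis.

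**The concern.** The validity of GEE inference grows with the number of independent clusters, and here each patient is one cluster. Six readings per patient give up to 216 observations (6 × 36) but only 28 to 36 independent units.

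The usual GEE output pairs a robust (sandwich) variance with a Wald chi-square test. With so few units that variance is somewhat too small. More importantly, the chi-square reference treats an estimated covariance matrix as if it were known. The error this causes grows with the number of parameters tested together. If time is categorical, a group difference in the course of pain over six readings is a 5-df test, which is where the problem is worst.

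At stake is a claim that the injection changes the course of pain over the first three days. It could be declared at P < .05 about two and a half to more than three times as often as the stated rate when there is no such effect.

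**Working it through.** **Inputs.** From Sample size: "alpha value = 0.05, 2-sided"; a difference in means of 5.0 − 2.5 = 2.5 VAS points; a common SD of 2.5; equal allocation; 14 evaluable and 18 randomised per group. From Data capture: six readings. Assumed, because the article does not give them: uncorrected robust variance, Wald chi-square reference, categorical time, complete data.

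**The plan's own figures.** Dropout: 14 / 0.8 = 17.5, so 18 per group, as stated. The 14 itself is not reproduced from the two-sided inputs: 2 × (1.960 + 0.842)² × (2.5/2.5)² = 15.7, so 16 per group, or 17 with the t distribution. That is a separate matter. Both values lie between the 14 and 18 used below.

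**Formula.** With a saturated group-by-time model, identity link and complete normal data, the result is exact. For n per group, v = 2n − 2 and p df:
- The robust variance divides by n instead of n − 1, so W = T² × n/(n − 1), where T² is Hotelling's statistic.
- T² × (v − p + 1)/(v p) follows F(p, v − p + 1).
- The Wald test rejects when W exceeds the chi-square critical value: 3.841 (1 df) or 11.070 (5 df).

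**Joint group-by-time test, 5 df.**
- n = 14: T² > 11.070 × 13/14 = 10.280; F = 10.280 × 22/130 = 1.740 on (5, 22) df; error 16.7%.
- n = 18: T² > 11.070 × 17/18 = 10.455; F = 10.455 × 30/170 = 1.845 on (5, 30) df; error 13.4%.

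**Single contrast, 1 df** (average difference or linear slope).
- n = 14: t² > 3.841 × 13/14 = 3.567 on 26 df; error 7.0%.
- n = 18: t² > 3.841 × 17/18 = 3.628 on 34 df; error 6.5%.

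**Which part causes it.** The standard error ratio is √(13/14) = 0.964 or √(17/18) = 0.972, a shortfall of 3.6% or 2.8%. Using an unbiased variance but keeping chi-square gives:
- n = 14: F = 11.070 × 22/130 = 1.873; error 14.0%.
- n = 18: F = 11.070 × 30/170 = 1.954; error 11.5%.

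So of the excess of 11.7 points at n = 14, the variance accounts for 2.7 and the reference for 9.0. At n = 18 the excess is 8.4 points, split 1.9 and 6.5.

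**Simulation check.** No effect; normal, bounded-VAS and skewed data; exchangeable correlation 0.5 or autoregressive 0.7 (all assumed); 8,000 trials each.

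| Test | 14 per group | 18 per group |
|---|---|---|
| Robust Wald, 5 df | 14.8–17.4% | about 11–13.7% |
| Robust Wald, 1 df | 6.3–7.4% | 5.9–6.8% |
| Hotelling-type F, 5 df | 3.4–5.2% | 3.5–5.4% |
| t test on each patient's average | 4.4–5.2% | 4.7–5.1% |

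Fitted GEE models (exchangeable, 1,000 trials) gave 17.9% and 12.6% for the robust 5-df test. With a bias-reduced variance and chi-square kept, they gave 11.4% and 9.3%.

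**An apparent remedy that falls short.** A mixed model with unstructured covariance and Satterthwaite df compares T²/5 with F(5, v).
- n = 14: critical value 2.587; 5 × 2.587 × 22/130 = 2.189 on (5, 22) df; error 9.2%.
- n = 18: critical value 2.494; 5 × 2.494 × 30/170 = 2.200 on (5, 30) df; error 8.1%.

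**The case against.** The strongest reply is that the article fixes neither the robust variance nor a joint test. Such options are commonly left to an analysis plan, which is not shown. Fitted model-based standard errors with a correct working correlation gave 6.0% and 4.9% (1 df) and 4.7% and 4.1% (5 df) at 14 and 18 per group, so no material inflation. This stands as a condition on the size of the problem. It is not a safe way out, because those errors depend on the working correlation being right. In simulation with assumed autoregressive correlation of 0.7–0.8, an exchangeable working structure with model-based errors rejected a linear group-by-time contrast in about 20–21% of null trials and the 5-df test in about 6–8%. Robust errors are the usual protection against that, and they bring back the 13–17%. What is questioned is the fit of a stated large-sample method to a stated small sample, not the absence of detail.

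Four stronger readings might be inferred, and the documents do not support them:
- *Every planned GEE test runs far above 5%.* The 1-df contrasts run at about 6.5–7%, a mild excess, and a linear time trend is itself a 1-df test.
- *The primary result is compromised.* One average per patient can be tested by the t or Mann–Whitney test already in Data analysis, and the t test held 4.4–5.2%.
- *The same rates apply to analgesic consumption.* Sufentanil use is defined over 48 hours without a stated grid of repeated measurements, so no rate was derived.
- *The expected 20% dropout invalidates GEE because data must be missing completely at random.* Data analysis plans multiple imputation above 10% missing, which removes that requirement.

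**Conclusion.** The point holds in conditional form, for pain over time only. If the GEE is run with the usual uncorrected robust variance and Wald chi-square tests, the joint 5-df group-by-time test has a true error rate of 16.7% with 28 patients and 13.4% with 36. Across the simulated distributions the range was about 11–17%. The chi-square reference is the main cause. Standard errors that are 3–4% short are the lesser one.

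The result assumes categorical time, complete data and a saturated group-by-time model. The rates are exact for normal data and were checked by simulation otherwise. This is a weakness in a non-primary analysis that is worth correcting before the data are analysed.

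**What to change.** In Data analysis, for VAS over time, replace the GEE chi-square test by a finite-sample analysis:
- Take the average 6–72 h group difference, and any time trend chosen in advance, as 1-df contrasts with a t reference.
- Test group-by-time with a Hotelling-type (multivariate repeated-measures) F test, or with a mixed model that adjusts both the covariance and the denominator df for small samples. Do not rely on unstructured covariance with Satterthwaite df alone for the 5-df test (8–9%).
- If GEE is kept, require a bias-corrected variance together with t/F references. Correcting the variance alone leaves about 9–11% on the joint test.
- For consumption, state the repeated measurement times if a model over time is intended, and apply the same small-sample rule.

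**Cost.** A few sentences of wording and no new data. The t interval for a 1-df contrast is wider than the uncorrected one by 2.056/(0.964 × 1.960) = 1.09 at 14 per group and 2.032/(0.972 × 1.960) = 1.07 at 18, so 7–9%. The joint test loses some power. The multivariate F test needs complete rows, so pooling over imputed data sets must be described. Whether the named SPSS version offers the adjusted mixed model should be checked before that option is written in.

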### Primary outcome measures

2.15

The primary outcome was the average pain score over the incision site from the time of surgery up to 3 postoperative days after surgery

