### Criteria for discontinuation

2.19

Every effort will be made to retain patients in the trial and to minimize withdrawals. However, the trial will be discontinued on condition that any SAEs happen. Additionally, patients may request to be withdrawn from this study at any time without any reason. Intention to treat and “as treated” analyses will be performed.

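### Median imputation below 10% missing understates error (arm medians) or shrinks the effect (pooled medians); analysis sets are offered as a missing-data remedy, which they are not.

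*Protocol article*

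**What the plan says.** Data analysis (2.21) sets a three-part rule:

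- Continuous and ordinal variables, low missingness: "For missing data less than 10%, imputation will be performed using median for continuous and ordinal variables".
- Nominal variables: "For nominal variables, the most common category will be imputed".
- Higher missingness: "If there are more than 10% missing data, multiple imputation will be used".

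It does not say whether the median is arm-specific or pooled, or whether the 10% is counted over patients, readings or variables.

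The same section then states: "Intention-to-treat and per-protocol analyses will be performed to account for possible missing data". Criteria for discontinuation (2.19) names a different pair: "Intention to treat and “as treated” analyses will be performed".

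The rule would act on the primary outcome, defined in 2.15: "The primary outcome was the average pain score over the incision site from the time of surgery up to 3 postoperative days after surgery". That average is built from six readings per patient, taken at 6, 12, 24, 36, 48 and 72 hours.

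**The concern.** Filling a gap with a single median and then running the planned Student t test counts a guess as a measurement. What goes wrong depends on a detail the text leaves open.

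- **Median within arm.** Each filled value sits at the centre of its own arm. The estimated difference is unaffected, but the SD is too small and the sample size is counted as full, so the reported standard error is too small and false positives rise.
- **Median over both arms.** Each filled value sits between the arms. The error rate is about right, but the estimated difference is pulled toward zero.

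The mode rule for nominal variables has the same weakness. For a side effect that most patients do not have, every missing record becomes no event.

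The wording on analysis sets is a separate and smaller matter. Intention to treat, per-protocol and as-treated decide which patients are analysed and in which group. None of them supplies or models an unobserved value, and leaving out protocol deviators can add selection. At stake are the calibration of the primary comparison at low missingness, and whether a reader can tell which supportive analysis was promised.

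**Working it through.** The plan gives no figure for the effect of its imputation rule, so there is none to reproduce. The check takes the plan's own design values and asks what the rule does to them.

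**Inputs from the protocol.** 18 per arm, 36 in total; SD 2.5; difference 5.0 − 2.5 = 2.5 (Sample size, 2.17); test level given as "alpha value = 0.05, 2-sided"; Student t test (2.21).

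**Assumptions not in the protocol.** Normal scores, one value per patient, values missing completely at random.

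**Range of the rule.** 3/36 = 8.3% and 4/36 = 11.1%, so if whole patients are lost the median rule covers at most k = 3 missing.

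**Arm medians, by approximation.** Filled values at the arm's centre add almost no spread, so the sum of squares carries 34 − k degrees of freedom but is divided by 34.

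- Reported SE ≈ 2.5 × √[((34 − k)/34) × (2/18)]
- True SE ≈ 2.5 × √[4/(36 − k)]
- The nominal cut-off of 2.032 (t, 34 df) then acts as 2.032 × reported/true.

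| k | Reported SE | True SE | Effective cut-off | Two-sided error |
|---|---|---|---|---|
| 1 | 0.821 | 0.845 | 1.974 | 5.7% |
| 2 | 0.808 | 0.857 | 1.916 | 6.4% |
| 3 | 0.796 | 0.870 | 1.858 | 7.3% |

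**Pooled median, by approximation.** With equal arms the pooled median lies near the midpoint, so each filled value is off by half the difference D. On average k/2 of the 18 values in each arm are filled. Each arm mean therefore moves by (k/36) × (D/2), and the difference becomes D × (1 − k/36):

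- k = 1: 2.5 × 35/36 = 2.43
- k = 2: 2.5 × 34/36 = 2.36
- k = 3: 2.5 × 33/36 = 2.29

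**Simulation.** Several independent runs of 20,000 to 60,000 trials per scenario agree with the approximations; ranges show the spread between runs.

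| k | Arm median: error | Pooled median: error | Pooled median: estimate of 2.5 | Observed values only: error |
|---|---|---|---|---|
| 1 | 5.7–5.8% | about 5% | 2.43 | about 5% |
| 2 | 6.3–6.5% | about 5% | 2.36 | about 5% |
| 3 | 7.2–7.5% | about 5% | 2.28–2.29 | about 5% |

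At k = 3 with a true difference of 2.5, the arm-median rule reports a mean SE of 0.79 against a true 0.87, and its 95% interval covers 92.7% of the time. Coverage is 94.3% with pooled medians and 95.1% with observed values only. The observed-only estimate stays at 2.50. The mode rule for nominal variables was not simulated.

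**Analysis sets, side by side.** Section 2.19 pairs intention to treat with as-treated; section 2.21 pairs it with per-protocol. As-treated regroups patients by what they received; per-protocol drops deviators. Both sections list intention to treat first. Neither says that all three will be run, and only 2.21 links the sets to missing data.

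**The case against.** The strongest reply is that the rule has little reach. It stops below 10%. The Sample size section plans for 20% dropout, about 7 of 36 patients (0.20 × 36 = 7.2), and missingness at that level would already fall under multiple imputation. This stands, and it limits the point to a moderate one.

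Second, the two harms are alternatives. A reader might infer that the plan both inflates false positives and dilutes the effect; it can do only one, depending on which median is meant. The text says only that a median is used, which fits a pooled median at least as well. On that reading the error rate is intact, the bias runs against the cocktail, and simulated power at 3 missing is essentially unchanged (79.3% against 79.1% for observed values only). What remains is a biased estimate.

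Third, one value per patient is a simplification. With six readings, time-specific medians and an assumed within-patient correlation of 0.5 to 0.7, three patients losing their last three readings gave an arm-median error of about 6.1–6.2% and a pooled estimate of about 2.39. However, 9% of readings missing at scattered times gave 7.3–7.7%, so the effect does not vanish.

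Fourth, observed-only analysis is no cure when loss depends on pain. With the three highest control scores removed and a true difference of 2.5, coverage was 85% for observed-only, 81% for arm medians and 78% for pooled medians. All fail, so the comparison favouring observed-only rests on values missing completely at random.

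Fifth, the 10% switch is fixed in advance. That the percentage is known only after data collection is true of any missingness rule and is not in itself analyst discretion.

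Finally, a reader might infer that 2.19 and 2.21 contradict each other, or that a favourable per-protocol or as-treated result could be passed off as the trial's answer. The documents do not support this. The three analyses can all be run, intention to treat is in both lists, and naming the deciding set is commonly left to an analysis plan that is not shown here.

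**Conclusion.** The concern holds as a moderate, wording-level fault in two parts.

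1. Single median or mode imputation below 10% is a poor rule as stated. Within arm, it takes the 5% error rate to about 5.8% at 1 missing and 7.2–7.4% at 3 missing, with a standard error roughly 9% too small (0.79/0.87 = 0.91). Pooled, it biases a difference of 2.5 to between 2.43 and 2.28. Leaving the values unimputed shows neither fault under the same conditions. The sizes rest on normal scores, one value per patient and values missing completely at random, and 3 of 36 is the top of the rule's range for whole-patient loss.
2. The statement that intention-to-treat and per-protocol analyses account for missing data is wrong as written. The different companion sets in 2.19 and 2.21 need reconciling, but they are a discrepancy rather than a contradiction, and nothing in the documents settles which of the two should be kept.

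**What to change.** In 2.21, drop median and mode imputation for outcomes, and with them the 10% threshold. Use one method at any level of missingness, either:

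- the multiple imputation already named; or
- a likelihood-based repeated-measures model on all observed VAS readings, which uses patients with only some readings without filling anything in.

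Multiple imputation is the smaller change, since the plan already commits to it above 10%. The repeated-measures model would have to be reconciled with the t test and the generalized estimating equation that 2.21 names.

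Delete the statement that the analysis sets account for missing data. Make 2.19 and 2.21 name the same analyses, with intention to treat as primary and any other set labelled supportive. Whether that is per-protocol, as-treated or both is for the sponsor to decide.

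The cost is a few sentences of wording and slightly wider intervals than arm-median imputation would report. No extra data or patients are needed.

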### Ethics and dissemination

2.22

The study has been approved by the Ethics Committee of Peking Union Medical College Hospital. This trial is registered with the Chinese Clinical Trial Registry (ChiCTR-IPR-17013094). On completion of the trial, the findings will be analyzed and tabulated. Results of the trial will be submitted for publication in a peer-reviewed journal.

## Discussion

3

To maximize postoperative pain relief, enhance patient satisfaction, and facilitate rehabilitation after surgery, pain management is indispensably important. Multimodal analgesia for pain management after surgery has been shown effective.^[5]^ However, no optimal regimen for pain control after spine surgery has been found. Therefore, we design a novel multimodal analgesic regimen for wound infiltration. Ropivacaine is a propyl analog of bupivacaine with longer duration of action and reversibly inhibits sodium ion influx in nerve fibers. It has lesser proclivity to penetrate large myelinated motor fibers compared with bupivacaine due to its low lipophilic nature. This is responsible for differential sensory blockade of ropivacaine with less central nervous system and cardiac toxicity compared with bupivacaine.^[18]^ Parecoxib is a selective COX-2 inhibitor shown to be as effective as traditional NSAIDs as an analgesic for acute postoperative pain whilst having fewer gastrointestinal side effects than traditional NSAIDs, such as diclofenac and ibuprofen.^[19–21]^ Moreover, parecoxib has no effects on serum thromboxane and platelet functions, suggesting that it may be an effective postoperative analgesic.^[22]^ Betamethasone produce strong anti-inflammatory action. This study hypothesized that cocktail analgesic injection could provide superior postoperative analgesia after lumbar spinal fusion surgery. In addition, this route of administration is safe, convenient, and general-purpose way in practice. To date; however, no comparative data are available. Therefore, we believe that this study will provide some insight into perioperative multimodal analgesia, which helps to improve perioperative clinical practice.
